### Clinical data

Clinical data include demographics of recipient and donor, immunologic parameters like HLA match and pre-formed antibodies, calculated GFR at the time of biopsy, any relevant diagnoses of the allograft like hydronephrosis or delayed graft function, any relevant factors at the time of biopsy which are potential confounders of the mass spectrometry test. These include CMV and polyomavirus infection, urinary tract infection, diabetes mellitus, hypertension, and the patient’s medication and immunosuppressive therapy.

### Outcome measures

The co-primary outcomes are sensitivity and specificity of the marker set for the diagnosis of acute rejection in the whole study population to determine the diagnostic accuracy of the marker set. These measures definitely determine whether the performance of the index test is sufficient to be used for the acute rejection diagnosis in comparison to the gold standard ‘renal allograft biopsy’.

Key secondary outcomes are *(i)* predictive values in terms of acute rejection in the whole study population and *(ii)* sensitivity, specificity and predictive values in subgroups. The subgroup analysis will help to determine the limits of the index test. This refers particularly to effects of confounding factors or conditions on the performance of the test and to the question which types and severity grades of acute rejection (in histological and functional terms) are detected with confidence.

### Statistical issues

#### Sample size

The primary objective of the trial is to show that mass spectrometry is not relevantly inferior to the gold-standard allograft biopsy. The null hypothesis of the study is that sensitivity and specificity of mass spectrometry are relevantly reduced compared to the gold standard biopsy. Thresholds are set to 83 % for sensitivity and to 70 % for specificity. Sample size calculation was done with nQuery 4.0, separately for sensitivity and specificity. The pre-test probability of acute rejection in kidney or kidney/pancreas transplanted patients with indication biopsy is expected to be 25 % (Hannover Transplant Centre Data; unpublished). The estimators of the test set of the previous phase II study are 91 % for sensitivity and 76 % for specificity. For both sample size calculations a one-sided χ^2^-test for single-proportion is used, assuming a one-sided type one error of 2.5 % and setting the power to 80 %. For a sensitivity of 83 % under the assumption of a true sensitivity of 91 %, 150 patients with acute rejection are needed, for a specificity of 70 % under the assumption of a true specificity of 76 %, 440 patients without acute rejection are needed. So, assuming the pre-test probability of 25 %, in sum a total sample size of 600 patients should be sufficient, where the patients with acute rejection (150 as 25 % of 600) determine the overall required number of patients.

No adjustment for multiplicity is necessary for testing sensitivity and specificity because both hypotheses have to be rejected, if the study should be evaluated as success. Loss to follow-up will not affect the analysis of primary and secondary outcomes because all necessary data for these calculations are collected at the time of urine sampling and renal biopsy on day 1 of the study.

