Beside the small sample sizes in these studies there are some further limitations. The histological scoring among the different studies is not uniformly conducted according to the BANFF classification [7, 9]. Partially, histological confirmation of the absence of rejection in the test-negative patients is missing (leading to the so called differential verification bias). Another important limitation is that, due to the small sample sizes, effects of potential confounders, like infectious conditions or different immunosuppressive regimens, are unknown.

Extending our proof-of concept study on 26 patients with acute tubulointerstitial rejection [10], we started out to refine and standardize the sample processing and analysis [13]. The resulting peptide pattern was validated in a cohort of 25 patients with and 43 patients without rejection. The AUC value was calculated to be 0.89 (95 % CI: 0.80 – 0.95). In a replication with a blinded test set of 17 independent patients, 6 of 7 patients with acute rejection were correctly classified as having rejection and 10 of 11 samples were correctly classified as negative for rejection (AUC: 0.83; 95 % CI: 0.57-0.96).

Moreover, we were able to identify the sequences of four peptides of the rejection pattern and found that three are fragments of the collagen type I alpha(I) (Col1A1) whereas the other is collagen type I alpha(III) derived. Similar results with changes of Col1A1 fragments in acute renal allograft rejection have been reported very recently [12]. In our peptide pattern, two of the Col1A1 fragments were less abundant in the rejection samples and one was increased. Aligning these fragments to other, commonly found Col1A1 peptides in the urine samples, we found that the increased peptide (ID-114633) possess a PGP motif at the c-terminal end which is indicative of increased matrix degradation by MMP-8 and MMP-9. Double-stains of the biopsies for MMP-8 and for an endothelial cell marker revealed confinement of MMP-8 to polymorphonuclear leukocytes located within pertubular capillaries and sparsely, in the interstitial infiltrates and glomerular capillaries of biopsies with rejection [13].

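### The planning values of 91% sensitivity and 76% specificity are credited to a test set that, as the article reports it, gave 6/7 = 85.7% and 10/11 = 90.9%, so the 80% power for sensitivity is conditional on an unsupported input

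*Protocol article*

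**What the plan says.** Under Sample size, the protocol article names where its planning values come from: "The estimators of the test set of the previous phase II study are 91 % for sensitivity and 76 % for specificity". It then sets the null values, "Thresholds are set to 83 % for sensitivity and to 70 % for specificity", and applies a one-sided single-proportion χ² test, "assuming a one-sided type one error of 2.5 % and setting the power to 80" per cent. This gives 150 patients with acute rejection and 440 without. At a pre-test probability of 25% the total is 600, and the section says that the patients with rejection determine it. Both hypotheses must be rejected for the study to succeed.

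The Background reports the earlier data in two parts. The refined peptide pattern was "validated in a cohort of 25 patients with and 43 patients without rejection", and the result is given only as an AUC of 0.89. The second part opens with "In a replication with a blinded test set of 17 independent patients". For sensitivity, the count given there is "6 of 7 patients with acute rejection were correctly classified as having rejection". For specificity, the corresponding count is "10 of 11 samples were correctly classified as negative for rejection". No other test set appears in the article.

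**The concern.** The Sample size section and the Background both appear to describe the test set of the earlier work, and they disagree on both measures. The planned sensitivity is about 5 points above the reported one. The planned specificity is about 15 points below the reported one.

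The sensitivity value matters most. It alone produces the 150 rejections, and so the total of 600. The margin over the 83% threshold is 8 points at a true 91% but only 2.7 points at 85.7%. Because sensitivity and specificity must both succeed, weak power for sensitivity cannot be offset by a strong result for specificity.

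**Working it through.** **1. The plan's own figures.** Inputs from Sample size: p0 = 0.83 and p1 = 0.91 (sensitivity), p0 = 0.70 and p1 = 0.76 (specificity), one-sided α = 0.025, power 0.80. The one-sample formula is

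n = [(1.960·√(p0(1−p0)) + 0.842·√(p1(1−p1))) / (p1−p0)]²

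- Sensitivity: (0.736 + 0.241)/0.08 = 12.21; squared, 149.2, so 150. Matches.
- Specificity: (0.898 + 0.359)/0.06 = 20.96; squared, 439.3, so 440. Matches.
- Total: 150/0.25 = 600. Matches.

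The arithmetic is right, given 91% and 76%.

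**2. The named source.** Inputs from Background:

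| Measure | Test set as reported | Exact 95% CI | Planning value |
|---|---|---|---|
| Sensitivity | 6/7 = 85.7% | 42% to 99.6% | 91% |
| Specificity | 10/11 = 90.9% | 59% to 99.8% | 76% |

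The possible values around 91% with 7 patients are 6/7 = 85.7% and 7/7 = 100%. Those around 76% with 11 are 8/11 = 72.7% and 9/11 = 81.8%. A denominator of 10 (17 − 7) does not give 76% either. The planning values cannot come from these counts.

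**3. The other cohort (25 with, 43 without rejection).** In the stated roles it does not fit either: 22/25 = 88% and 23/25 = 92%; 32/43 = 74.4% and 33/43 = 76.7%, which rounds to 77%.

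**4. How much depends on 91%.** With 150 rejections, the planning test rejects from 134 correct classifications upward, since (134/150 − 0.83)/√(0.83·0.17/150) = 2.07, while 133 gives 1.85. The Wald rule in Statistical analysis rejects from 133 upward: its lower limit is 83.6% at 133 and 82.8% at 132. Exact binomial power, with the n that the formula in step 1 needs for 80%:

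| True sensitivity | Power, planning test | Power, Wald rule | n with rejection for 80% |
|---|---|---|---|
| 91% | 81% | 87% | 149.2 |
| 90% | 67% | 76% | 199.5 |
| 88% | 36% | 46% | 407.8 |
| 85.7% | 12% | 18% | 1,442.1 |

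**5. Does 6/7 refute 91%?** No. At a true 91%, the chance of 6 or fewer correct out of 7 is 1 − 0.91⁷ = 0.48.

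**6. Specificity.** If 10/11 is close to the truth, power with 450 patients without rejection is above 99.9%. This side is not threatened.

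**7. Test-set size.** 7 + 11 = 18 results against 17 patients.

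**The case against.** The best defence is that the source is not pinned down. Sample size gives no reference for the phase II study. Background attaches the phase 1 and 2 label to a group of references that does not include the one for the refined pattern. Index test derives the cut-off of −0.25 from the proof-of-concept study, while Background does not say which cut-off produced 6/7 and 10/11. Another dataset or cut-off may lie behind 91% and 76%, and a full protocol might say so. The 80% power is also openly conditional on an assumed 91%.

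Part of this stands: the discrepancy may have an innocent explanation, and no calculation is wrong. It does not remove the point. Background says that the test under study is the refined one, and the article describes only one test set for it. This is not detail left to a fuller document: the article prints both sets of figures, and they conflict.

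A reader might infer three stronger things, none of which the documents support:

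- **That power is really 12%, or that about 1,440 rejections are needed.** This treats 6/7 as the truth. The interval of 42% to 99.6% and the 48% chance in step 5 rule that out.
- **That sensitivity and specificity were swapped.** The reported specificity does round to 91%, and in the 25/43 cohort 19/25 = 76% and 39/43 = 90.7% fit with the roles exchanged. But pooling the cohort with the test set fits equally well as printed: 29/32 = 90.6% and 41/54 = 75.9%. Matching fractions cannot decide between these, and a pooled estimate would not be a test-set estimate.
- **That 17 against 18 undermines the sensitivity.** The text counts patients in one place and samples in another, so one patient may have given two samples. The 6/7 is unaffected.

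**Conclusion.** The point holds as a contradiction about where the planning values come from. The article credits 91% and 76% to a test set whose reported counts cannot give either value, and it reports no other data that yield them. The 150 rejections and the total of 600 therefore rest on a sensitivity with no support in the article, and the 80% power is valid only if 91% happens to be true.

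The true power is unknown. A drop of 1 point in true sensitivity takes exact power under the planning test from 81% to 67%, and a drop of 3 points takes it to 36%. The Wald rule gives 87%, 76% and 46%. These figures assume exactly 150 patients with rejection.

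The conclusion rests on reading the test set in Sample size as the one in Background, which is the only one described. The thresholds, the decision rule and the type I error do not depend on the planning value.

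**What to change.** - State the dataset, the counts and the cut-off that gave 91% and 76%, and correct Sample size or Background accordingly. While tracing them, check whether the two values were interchanged or came from pooled cohorts; neither is established.
- If the Background figures are the test-set estimates, present 91% as a planning assumption with its own justification. Replace the single 80% with power for sensitivity over a range of true values, such as the table above.
- As a minor point, reconcile 17 patients with 7 + 11 results, saying whether one patient gave two samples.

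The cost is a text correction. The stated power may look less favourable. No patients are added, and the thresholds and decision rule stay as they are.

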#### Methods against bias

Biopsy and mass spectrometry will be performed independently by different readers. Readings must have reference to the medical history of the patients, but diligence will be exercised that knowledge of the results of the other test is withheld. For this reason, results of the experimental test will not be provided for patients and examiners that perform the gold standard test until the end of the study.

In addition to the local biopsy reading in each centre, biopsies will be re-evaluated centrally to confirm the interpretation of the biopsy. The index test is conducted according to a pre-assigned SOP (for details see Additional file 1).

Selection bias in the patient recruitment is negligible because the inclusion and exclusion criteria enable the study of a representative cohort by consecutively including all patients with an indicated biopsy who agree to participate in the study. The primary analysis will be confined to the indication biopsy and concomitant urine sample which were taken at day 1 of the study. Repeated urine collections from one patient will be not included into the primary analysis to avoid dependent data in a setting of independent observations from individual patients.

To assess the possible measurement error of the mass spectrometry, 10 % of the urine samples (randomly chosen) will be re-run including all sample preparation steps. In the secondary analysis, the results of these probe pairs will be used to evaluate the test reproducibility.

Impact of centre on the results will be examined in the statistical analysis.

#### Statistical analysis

For the primary analysis, point estimators and two-sided 95 % Wald confidence intervals for sensitivity and specificity will be calculated. The null hypothesis for sensitivity will be rejected if the lower bound of the corresponding confidence interval is above 83 %. The null hypothesis for specificity will be rejected if the lower bound of the corresponding confidence interval is above 70 %.

For the key secondary analyses, predictive values for all patients and sensitivity, specificity and predictive values for subgroups will be analysed descriptively. Subgroups are: patients with different BANFF grades of acute rejection; patients with different severity of acute rejection in terms of functional impairment at the time of rejection; patients with kidney allografts alone and patients with combined kidney/pancreas transplantation; patients from each transplant centre; patients with concurrent urinary tract infection at the time of biopsy/urine sampling; patients with concurrent CMV infection at the time of biopsy/urine sampling and patients with polyomavirus nephropathy.

Furthermore, the secondary analysis examines whether certain clinical, laboratory or pathological variables interfere with the mass spectrometric test. This facilitates the search for potential confounders and the definition of the limits of the MS test.

For the primary analysis no missing data due to drop-outs is expected because once a patient has consented to participate in the study the data for primary analysis is available. Drop-outs would only affect analysis of follow-up data (e.g. rejection events after the test).

Within the sensitivity analysis, the clinical course and subsequently performed biopsies (if available) will be additionally used for an assessment of the probable true disease state in case of a positive mass spectrometry result and a negative biopsy. Also, the results of the central read of the biopsy vs. the local pathological diagnosis will be used in the sensitivity analysis.

In a descriptive secondary analysis, the test reproducibility will be evaluated. Therefore, Krippendorff’s alpha will be calculated for the probe pairs (of 10 % of the patients).

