**Design and methods:**

The aim of this study is to examine the diagnostic accuracy of mass spectrometry analysis in urine for the diagnosis of acute rejections using the biopsy as gold-standard. The study is an ongoing prospective, single-arm, multicentre, phase 3 diagnostic accuracy study. It started in October 2011 and will be concluded in December 2015. Patient within the first year after transplantation who are scheduled for a biopsy to clarify unexplained impairment of the allograft are consecutively recruited into the study. The overall sample size (n = 600) was calculated to demonstrate a sensitivity of 83 % and a specificity of 70 % for a one-sided type one error of 2.5 % and a power of 80 % per hypothesis. Biopsy evaluation and mass spectrometry analysis of urine samples (obtained immediately before biopsy) are performed independently by different readers without knowledge from the respective other assessment. The follow-up observation period is 6 months. For the primary analysis, the lower limits of the two-sided 95 % Wald confidence intervals for sensitivity and specificity will be compared with the pre-specified thresholds (83 % for sensitivity and 70 % for specificity). In secondary analyses the predictive values, the diagnostic measures in subgroups, and the clinical course will be assessed.

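### The Wald lower limit that decides success gives sensitivity a false-success rate of about 4%, not the stated one-sided 2.5%, and is not the χ² test used for sizing

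*Protocol article*

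**What the plan says.** The *Statistical analysis* section of the protocol article states: "For the primary analysis, point estimators and two-sided 95 % Wald confidence intervals for sensitivity and specificity will be calculated". Each null hypothesis is rejected when the lower bound lies above its threshold. The abstract (*Design and methods*) gives the same rule: "the lower limits of the two-sided 95 % Wald confidence intervals for sensitivity and specificity will be compared with the pre-specified thresholds".

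The *Sample size* section gives the thresholds ("Thresholds are set to 83 % for sensitivity and to 70 % for specificity") and the assumed true values ("The estimators of the test set of the previous phase II study are 91 % for sensitivity and 76 % for specificity"). For both calculations a one-sided χ² "test for single-proportion is used", "assuming a one-sided type one error of 2.5 % and setting the power to 80" %. The results are "150 patients with acute rejection are needed" and "440 patients without acute rejection are needed". With a pre-test probability of 25% this leads to 600 patients in total. The section waives any multiplicity adjustment because both hypotheses must be rejected.

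**The concern.** Two procedures are in play. The χ² test for one proportion uses the variance at the null value, p₀(1 − p₀)/n. The Wald limit uses the variance at the estimate, p̂(1 − p̂)/n. Both thresholds lie above 50%, so any estimate that could lead to success has a smaller variance than the null value has. The Wald lower limit is then too high and the test rejects too often. The effect grows towards 100%, so it should be larger at 83% with about 150 patients than at 70% with about 450.

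At stake is the trial's only confirmatory claim. The argument that no multiplicity adjustment is needed is sound only if each of the two tests holds its own 2.5% level.

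**Working it through.** **Inputs**, all from the *Sample size* section: p₀ = 0.83 and p₁ = 0.91 for sensitivity; p₀ = 0.70 and p₁ = 0.76 for specificity; one-sided α = 0.025; power 0.80; prevalence 0.25; N = 600, hence 150 expected with rejection and 450 without.

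**1. Reproduce the stated sample sizes.** For the χ² (score) test,

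n = [(z₀.₉₇₅√(p₀(1 − p₀)) + z₀.₈₀√(p₁(1 − p₁))) / (p₁ − p₀)]²

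- Sensitivity: [(1.960 × 0.3756 + 0.8416 × 0.2862) / 0.08]² = 149.2, so 150.
- Specificity: [(1.960 × 0.4583 + 0.8416 × 0.4271) / 0.06]² = 439.3, so 440.

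Both match the article. With the variance at p₁ in both terms, as a Wald test would have it, the formula gives 101 and 398. The trial was therefore sized on the score test.

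**2. Find the smallest successful count at n = 150.** The Wald limit is p̂ − 1.960√(p̂(1 − p̂)/n). The score statistic is (p̂ − 0.83)/√(0.83 × 0.17/150), and its denominator is 0.03067.

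| Correct among 150 | p̂ | Wald lower limit | Score statistic | Wilson lower limit |
|---|---|---|---|---|
| 132 | 88.0% | 82.8% (fail) | 1.63 (fail) | 81.8% (fail) |
| 133 | 88.7% | 83.6% (success) | 1.85 (fail) | 82.6% (fail) |
| 134 | 89.3% | 84.4% (success) | 2.07 (success) | 83.4% (success) |

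**3. Exact error and power.** The error is P(X ≥ cut) for X ~ Binomial(n, p₀), and the power is the same tail at p₁.

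| | Cut | Error at p₀ | Power at p₁ |
|---|---|---|---|
| Sensitivity, n = 150, Wald | 133 | 3.61% | 87.1% |
| Sensitivity, n = 150, score or Clopper-Pearson | 134 | 2.07% | 80.7% |
| Specificity, n = 450, Wald | 334 | 2.73% | 82.6% |
| Specificity, n = 450, score or Clopper-Pearson | 335 | 2.12% | 79.7% |

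At exactly 440 patients without rejection, Wald and score share the cut 327 and the error 2.59%.

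**4. Let the number of rejections vary.** It is not fixed by design, so average over Binomial(600, 0.25) for those with rejection and Binomial(600, 0.75) for those without.

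| Average error (average power) | Wald | Score | Clopper-Pearson |
|---|---|---|---|
| Sensitivity | 4.19% (88.3%) | 2.09% (80.4%) | 1.92% (79.3%) |
| Specificity | 2.92% (83.4%) | 2.38% (81.0%) | 2.20% (80.1%) |

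For sensitivity the Wald error exceeds 2.5% at every count from 130 to 170, ranging from 3.1% to 5.3%. It is not an artefact of one n.

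**5. Trial-level false success with true sensitivity 83%.** Both hypotheses must be rejected, so this is approximately the sensitivity error times the power for specificity.

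- True specificity 76%: Wald 0.0419 × 0.834 = 3.5%; score 0.0209 × 0.810 = 1.7%.
- True specificity 80% or more: Wald about 4.2%; score about 2.1%.
- True specificity 70%: Wald 0.0419 × 0.0292 = 0.12%.

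**The case against.** The best defence is that Wald is an openly pre-specified large-sample method and that 2.5% is its nominal level. All approximate binomial methods miss nominal at some n. The score rule itself reaches 2.7% at some counts between 130 and 170. At 150 rejections the two rules disagree on a single result, 133/150; over 130 to 170 they differ by one or two patients. Specificity is close to nominal. The trial-level rate is below the sensitivity figure unless specificity is well above its threshold. The mismatch with the sizing does not leave the trial underpowered, because Wald has more power, not less.

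Much of this is true and limits the point. The material inflation is confined to sensitivity, 4.2% is the worst case for the trial, and the mismatch with the χ² test does no harm beyond the type I error. But the score rule scatters around or below 2.5% and averages 2.1%. The Wald rule lies above 2.5% throughout the plausible range and averages twice as much. At the protocol's own assumed specificity of 76% the joint rate is still 3.5%. The extra power, 87.1% against 80.7%, is bought with the extra error.

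**Conclusion.** The point holds. The primary decision rule does not keep the one-sided 2.5% that the same article states. For sensitivity the false-success rate is 3.6% at 150 rejections and 4.2% averaged over their random number. The test used for sizing gives 2.1% in both cases. For specificity the excess is small (2.9% on average). Since both must be rejected, the trial's false-success rate at a true sensitivity of 83% is 3.5% if specificity is 76%, and about 4.2% once it is 80% or more.

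These figures assume 600 evaluable patients, a prevalence of 25% and independent binomial outcomes. The article names no interval method for the descriptive subgroup analyses, so the point does not extend to them.

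**What to change.** In *Statistical analysis* and in the abstract, replace the Wald interval with the two-sided 95% Wilson score interval for both co-primary outcomes, leaving the thresholds as they are. The Wilson limit inverts the χ² test used for sizing, so analysis and sample size then agree. If the level must hold at every possible number of rejections, specify Clopper-Pearson instead; its average power is 79.3% for sensitivity and 80.1% for specificity.

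No extra patients are needed. With Wilson, power is 80.7% for sensitivity at 150 and 79.7% for specificity at 450 (80.4% and 81.0% on average). The cost is slightly less favourable lower limits and a dated amendment to the primary analysis of a running trial. The *Study design* section keeps the mass spectrometry results concealed until the end of the study, so the amendment can be made without knowledge of them. It should be signed off before they are disclosed.
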